The overall goal of the interventions is to reduce adolescent fertility in the long-run by improving the wellbeing of girls in programme sites. A randomized controlled trial will be used to compare the impact of four different packages of interventions. In the Nairobi study, randomization to the four study arms will occur at the individual level. In Nairobi the design also includes an external control site. In Wajir, approximately 80 clusters (school-catchment areas) will be randomized to the four study arms. The research design will use both qualitative and quantitative methods to evaluate this impact. The quantitative study will consist of a baseline survey before the intervention is implemented, randomization to intervention packages, a Midterm survey with the same girls after the two-year intervention, and an endline survey two years post-intervention. Biomarker data, including testing for anaemia, Human Immunodeficiency Virus (HIV) and Herpes Simplex Virus 2 (HSV-2), will be collected at midterm and endline in the Nairobi sample. In-depths interviews will be conducted with a sample of program participants and key stakeholders halfway through the intervention and one-year post-intervention to better understand the causal mechanisms and the strengths and weaknesses of the intervention implementation. In addition, careful costing data will be collected to understand the cost of each intervention.

Risks and Benefits

Primary ethical concerns of this study include a) that participation in the study may put the respondent at risk of psychological trauma related to recounting violent or traumatic experiences, b) that this study includes minors, below the age of 18, and c) a risk of breach of confidentiality due to the collection of contact information and identifying information for future survey rounds. These risks are perceived to be minimal and steps will be taken to reduce the risks to participants.

Participants will receive no compensation for their participation in the study. In intervention sites, participants will benefit directly or indirectly from project interventions. All participants will be providing information that will directly inform the development of the interventions for adolescent girls in Kenya.

1. **Study Relationships/Related Project**

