The main objectives of the research will be to determine: 1) Which combination(s) of interventions produce(s) the greatest change in the wellbeing of adolescent girls? and 2) What is the most cost-effective way to achieve the greatest impact for adolescent girls?

A randomized controlled trial design will be used to examine the impact of the intervention packages on various indicators of adolescent fertility and well being of girls over a four-year period (see Appendix A). The project will be implemented in Wajir County and Nairobi slums. Wajir County is located in the mainly rural, semi-arid region of Northern Kenya, and inhabited by a mainly pastoralist, Muslim population of Somali origin. The Nairobi slums represent the urban poor population of Nairobi. They are characterized by high population density, lack of public utilities and services, and high rates of migration.

In Nairobi, girls will be randomized to intervention packages at the individual level. All girls aged 11 to 14 residing within the study site will be listed and 3,000 girls will be selected based on a vulnerability index that excludes girls from high socio-economic status households. These girls will then be randomized to one of the four study arms. In addition, using the same procedure in an external control site, 750 girls will be interviewed but will not directly benefit from the interventions. In Wajir randomization will occur at the cluster level. Clusters will be defined as school-catchment areas of a fixed radius around a public primary school that includes all families sending girls aged 11 to 14 to the given public primary school. Based on power calculations, we will have 80 clusters (20 per arm), which will have approximately 3,200 girls in the given age group).

The intervention packages that will be tested are:

1. Violence Prevention
2. Violence Prevention + Education
3. Violence Prevention + Education + Health
4. Violence Prevention + Education + Health + Wealth Creation

The selection of package combinations was based on three factors: 1) prioritizing what component effects were important to isolate; 2) generating evidence on new interventions and new combinations of interventions for which there is none; and 3) testing packages with varying implementation costs.

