The hypothesis is that this diverse asset base, once acquired, will lead to increased educational attainment, delayed childbearing and marriage, fewer unintended pregnancies, less experience of violence, and increased economic assets. Using both quantitative and qualitative data, we will also test the causal mechanisms driving the impact for each of the four intervention sectors, based on the hypotheses shown in Appendix B.

1. **Intervention**

Population Council has been involved in the design of the interventions, but the interventions will be implemented by Save the Children (Wajir) and Plan International (Nairobi). Information on these implementing partners has been provided in Section 3. All interventions will be implemented for a period of two years in research sites (see timeline in Appendix C). The beneficiaries will be girls selected for the research study as per the procedures described in Section 8.

In each sector AGI-K will implement one intervention so that it will be possible to attribute any change to that specific intervention component. In cases where more than one component is proposed, the rationale and evidence will be provided.

1. Violence Prevention

The violence prevention intervention will be a community level intervention using the community dialogues and contracts strategy.

AGI-K will adapt the UNDP/Concern model (described below), integrating promising approaches from the PC Guatemala and East Africa activities and will run this component for the full two years of the AGI-K intervention. It is envisioned that a core committee will be established within the first month. The committee will comprise religious leaders, community leaders, parents, teachers, and young men and women. This group will go through a facilitated process where they learn to identify the key issues in the community that lead to the under-valuing of girls, come up with a “contract” of steps to address those issues, and then carry out activities to implement the contract over the course of the intervention. A small amount of funds will be available for each community for implementation of the agreed upon steps. Careful monitoring will be done of the committee meetings and committee-led activities.

Community Conversations Model

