**8. Data Collection Activity 6: Biomarker Data**

**a. Subject Population**

- The study population is 2, 394 girls aged 15 or older residing in Kibera (Nairobi), who participated in the Baseline Survey. At midline we anticipate this to be approximately half of the sample and at endline the full sample will be eligible.

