**11. Instrument Development**

The instruments were developed by the study investigators based on previous surveys, study outcomes and indicators to be tested and gaps in the literature. The household listing tool was developed based on previous tools used in Kenya and Zambia in studies of adolescent girls. The school quality tool is based on the Malawi School Quality survey and the Kenya Ministry of Education, Science and Technology school census tool for their Education Management and Information System. The quantitative survey for girls will cover topics such as: household socio-demographic characteristics; schooling history; education attainment: social assets and networks, self-efficacy, locus-of-control, financial literacy, savings and livelihoods, marital and child-bearing aspirations, birth history, experience of physical and sexual harassment and violence, attitudes on FGM, self-reported health and nutrition; reproductive health knowledge, HIV and AIDS risk perception; comprehension in local language and English; excerpts from official mathematics assessments multiple standards (grades); and cognitive testing. The midterm survey will include additional questions to measure exposure to interventions. The household background survey was developed using questions from the Kenya Demographic and Health survey on household assets and living conditions. Other questions were added from previous tools used in the Kenyan context. The purpose of this tool is to collect background information that the girls might not be privy to. The tool also includes some questions on gender norms that will be used to assess changes attributable to the community-level intervention over time. The surveys will be translated into Swahili and Somali. The surveys will be pilot-tested prior to the start of data collection and revised based on feedback from interviewers before data collection begins.

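### Violence prevention is in all four randomised packages, so the protocol cannot attribute change to that component: it is uncontrolled in Wajir and compared only with one non-randomised site in Nairobi

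*Protocol*

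**What the plan says.** The Background section of the protocol lists four nested packages. The first is violence prevention alone, and the last is "Violence Prevention + Education + Health + Wealth Creation". Violence prevention is in each of them. The Intervention section describes how it is delivered: "The violence prevention intervention will be a community level intervention using the community dialogues and contracts strategy".

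On allocation, the Summary of proposed research says: "In Wajir, approximately 80 clusters (school-catchment areas) will be randomized to the four study arms". The Background adds: "Based on power calculations, we will have 80 clusters (20 per arm), which will have approximately 3,200 girls in the given age group". The baseline survey section makes every catchment area in the Wajir study sites eligible. Nairobi girls are randomised individually to the same four packages. The only group outside the packages is mentioned for Nairobi alone: "In Nairobi the design also includes an external control site".

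Three statements claim more than this allocation gives:

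- The Intervention section: "In each sector AGI-K will implement one intervention so that it will be possible to attribute any change to that specific intervention component".
- The end of the Background, which promises a test of causal mechanisms in all four sectors, violence included.
- Section 11, Instrument Development, which says the household tool has "questions on gender norms that will be used to assess changes attributable to the community-level intervention over time".

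Appendix D gives the violence sector two key indicators of its own, experience of gender-based violence and gender norms related to violence.

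**The concern.** Crediting a change to a component needs a comparison between people who had it and similar people who did not. The randomised arms offer no such comparison for violence prevention. The protocol does not say so, and its wording points the other way.

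The statement in Instrument Development carries the most risk because it refers to change over time. In Wajir, following it would mean reading the movement in gender norms or reported violence between baseline and the later rounds as an effect of the community dialogues. The girls are 11 to 14 at baseline, in early 2015, and are interviewed again in 2017 and 2019. Reported violence can be expected to change over those ages without any programme, and norms can shift for reasons unrelated to it. A causal finding for one of the four sectors would then rest on uncontrolled change.

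**Working it through.** **1. The protocol's own allocation.** Wajir: 4 arms x 20 clusters = 80 clusters, which is the whole stated number, so no cluster is left without a package. Nairobi: 3,000 / 4 = 750 girls per arm as planned. The Monitoring Data section counts arms 2 to 4 as 2,250 = 3 x 750 in Nairobi and 2,400 = 3 x (3,200 / 4) in Wajir. The four arms therefore use up the whole randomised sample at each location.

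**2. What the randomised arms identify.** Write V, E, H and W for the four components and a for the mean without any of them. On an additive scale the arm means are:

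- arm 1: a + V
- arm 2: a + V + E
- arm 3: a + V + E + H
- arm 4: a + V + E + H + W

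The six pairwise differences are:

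| Contrast | Result |
|---|---|
| 2 - 1 | E |
| 3 - 2 | H |
| 4 - 3 | W |
| 3 - 1 | E + H |
| 4 - 2 | H + W |
| 4 - 1 | E + H + W |

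V cancels in all six. Equivalently, the design matrix with columns for intercept, V, E, H and W has rank 4 for 5 parameters, because the V column equals the intercept column. E, H and W are estimable as increments on the components below them; V is not. More girls or another model for the same arms does not change this.

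**3. Wajir.** There is no further row to add. The only quantity that bears on V is the change over time within arms. For arm 1 that change equals V plus the effect of ageing plus secular trend, and nothing in the design separates the three.

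**4. Nairobi.** The external site adds one row with mean a.

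- If the two sites are assumed not to differ apart from the programme, V becomes estimable.
- If a site term is allowed, V is not estimable again, because V and site take the same values in every row.

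So the estimate rests entirely on an assumption about sites. Differencing from baseline removes site differences that are constant over time, but not differences in trend between the two sites.

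**5. An illustration of the Nairobi limit.** The protocol gives no between-site variation, so the range here is assumed. Take 2,394 / 4 = 598.5 girls in arm 1 and 699 in the external site, reading Huruma as that site. With one site per side, in SD units,

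variance of the difference = 2 x ICC + (1 - ICC) x (1/598.5 + 1/699).

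The detectable difference at two-sided 5% and 80% power is 2.80 times its square root:

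| Assumed ICC | Detectable difference (SD) |
|---|---|
| 0 | 0.16 |
| 0.005 | 0.32 |
| 0.01 | 0.43 |
| 0.02 | 0.58 |
| 0.05 | 0.90 |

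The term 2 x ICC does not shrink as girls are added. For a difference-in-differences the ICC must be read as variation between sites in change over time. The data cannot estimate it with one site per side.

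**6. A further difference between the Nairobi sites.** The biomarker section defines its population as "girls aged 15 or older residing in Kibera (Nairobi), who participated in the Baseline Survey", and testing comes with counselling on safe sex. The Summary speaks more loosely of the Nairobi sample, but the biomarker count of 2,394 equals the Kibera count. Consent for testing comes after the interview, so midterm answers precede the counselling. Endline answers from girls tested at midterm follow it.

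**The case against.** The strongest reply is that the sentence in the Intervention section has been misread. The sentence after it promises a rationale wherever a sector has more than one component. Together the two read as a rule against bundling within a sector, not as a promise of a stand-alone randomised effect for each sector. The Background also says the packages were chosen partly by which component effects mattered most to isolate, which implies that some would not be. The stated objectives are to compare combinations and their cost-effectiveness, and the allocation serves them.

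Much of this stands. The bundling reading is plausible, and leaving violence prevention unisolated may well have been deliberate. But neither point covers the wording in Instrument Development, which concerns the community-level intervention itself and is not restricted to Nairobi. Nor do they cover the promised causal test in all four sectors. If the choice was deliberate, these statements contradict it.

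It is also fair to say that the estimator for the Nairobi comparison can be left to a statistical analysis plan. No analysis plan, however, can supply the missing contrast.

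A reader might infer more than the document supports:

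- *That attribution fails for arms 2 to 4 as well.* It does not. The packages are openly additive, and each increment is a randomised effect of the added component.
- *That the violence indicators have no randomised comparison at all.* They do. The health curriculum covers gender norms and gender-based violence, so arm 3 v 2 is informative on those indicators. Only the contribution of the violence component itself is missing.
- *That the two Nairobi sites are shown to be unlike, since 2,394 of 3,000 planned girls were reached in one and 699 of 750 in the other.* These compare achieved with planned counts. They are not response rates and say nothing about comparability.
- *That sexual-health outcomes should be moved to midterm because of the counselling.* That would discard the round that serves the long-run aim, for the sake of one non-randomised contrast. The randomised comparisons within Kibera do not carry this site difference.

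**Conclusion.** The point holds for violence prevention only. None of the six randomised contrasts isolates it at either location. In Wajir its effect is not identified. In Nairobi it is identified only by assuming that one intervention site and one external site would otherwise have changed alike. The attribution statements in the Intervention and Instrument Development sections are therefore wrong for this component.

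The weight is moderate: one of four sectors, with two of the key indicators, is affected. The objective of comparing packages, the three increments and the conduct of the trial are not.

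The conclusion follows from the list of packages and needs no numerical assumption. The range of 0.16 to 0.90 SD rests on assumed ICCs and on reading Huruma as the external site; it illustrates the limit and is not evidence for it.

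**What to change.** 1. In the Intervention section, limit the attribution statement to the randomised increments: education (arm 2 v 1), health (arm 3 v 2) and wealth creation (arm 4 v 3), each on top of the components below it. Put the same limit on the four-sector causal test at the end of the Background.
2. State that the effect of violence prevention is not identified in Wajir. Reword the gender-norm sentence in Instrument Development so that change over time there is descriptive only.
3. For Nairobi, label any arm 1 v external-site contrast as a non-randomised, baseline-adjusted difference-in-differences with one site per side, and do not use it for confirmatory claims.
4. For that external contrast only, note that endline sexual-health outcomes may also reflect the testing and counselling that the biomarker section limits to Kibera. Keep the endline for all randomised comparisons.

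No arm, sample or procedure changes. The cost is some wording, one label, and giving up a causal claim for the violence component.

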**8. Data Gathering Activity 1: Household Listing**

**a. Subject Population**

- In Nairobi urban slums, an initial household listing will take place in the study sites (TBD) with the assistance of maps obtained from KNBS and local village elders. The research team will screen and list all members of households within the selected sub-locations that have an adolescent girl between the ages of 10 and 15 (approximately 60,000 to 90,000 households). The respondents will be adults (age 18+) residing in each household. The household listing will allow us to identify eligible adolescent girls between the ages of 11 and 14 in each household. The listing form will also collect basic information on household characteristics that will be used to rate households using a vulnerability index.
- In Wajir County, data from the national Hunger Safety Net Program (HSNP), a conditional cash transfer program for vulnerable households in the arid and semi-arid lands of Kenya, will be used to provide the sampling frame. These data are from a program registration of all households in Northeastern Kenya in 2013. The Council has obtained a subset of the data for approximately 66,714 households with a girl between the ages of 7 and 14 in Wajir County. The data include information on heads of households, individuals’ ages, education attainment, health and household characteristics as well as village-level GPS coordinates. The Council has received permission from the National Drought Management Authority, the owners of the data, to use the data for the purpose described here.

**b. Research Protocol**

- The household listing will be conducted between October and December, 2014 in the study site in Nairobi slums. Maps of the structures in each enumeration area within the study site will be obtained from the Kenya National Bureau of Statistics prior to the activity. Trained research assistants will visit every household, identify an adult who can answer questions about members of the household, and interview them using a short form (see Annex 2) to collect the required information. They will begin by asking several screener questions. If there is at least one girl between the ages of 10 and 15 residing in the household, they will complete the household roster and the brief background questionnaire on household characteristics. Interviewers will make up to three visits to each household if there is no one present.

**c. Risks and Benefits to Subjects**

- There is a minimal risk of breach of confidentiality, since the household listing form includes contact information and identifies the location of the household. However, no sensitive information will be collected as part of the listing activity.
- The benefit of participating in the listing is that if there is a girl residing in the household, between the ages of 11 and 14, she will be eligible to participate in the study and may receive direct benefit from the interventions.

**d. Steps to Minimize Risks**

- To minimize the risk of loss of privacy, data will be collected using electronic data capture (tablets) and will be stored on password-protected computers at the Population Council office.

**e. Confidentiality**

- All data that includes identifying information will be stored on password-protected computers that will only be accessible by authorized research staff.
- Records will be kept throughout the life of the study and will be kept for up to 10 years afterwards to allow researchers to follow-up with the girls for future survey rounds if external funding is obtained.
- The information collected in the household listing activity will be used to evaluate characteristics of eligible households whose girls chose to participate in the interventions, and those that did not. This information will be provided at aggregate and no identifying information will be used.

**f. Compensation**

- The participants will not be paid for their participation in the household listing activity.

**g. Informed Consent Process**

- Verbal informed consent will be obtained at the time of the household listing. Interviewers will approach the household and read a brief statement (see Annex 1) explaining the purpose of the household listing, assuring respondents that participation is completely voluntary and that it is their right to refuse to answer any questions or stop the interview at any point. Written informed consent will not be collected for the household listing.
- Before the study commences, permission for the study will be obtained nationally by obtaining a research permit from the National Council of Science and Technology in Kenya. We will also obtain local IRB approval from the AMREF Ethical & Scientific Review Committee. Study coordinators will also make courtesy calls to local government officials, including the District/Sub-County Commissioner, the District/Sub-County Officer, and the chiefs in the selected sub-locations. The study team will work with village elders to identify areas in the community.

